### Randomisation and Blinding

Randomisation (intervention group or control group) will take place at the GP level and will be carried out centrally by the study centre. After the initial picture scoring sessions and the full day training course, we will draw up a randomisation list by computer (ralloc command of Stata software for Windows, Version 11). Blinding of the GPs is not possible.

### Training course

The GPs in both groups will receive a full day training course on skin cancer diagnosis which is going to be organized by [name] and his collaborators from the Department of Dermatology of the University Hospital Zurich. This training course will contain structured lectures and interactive problem based teaching.

### Time frame

The time frame of our study is shown in Figure 2. The study is intended to last around 16 months from which the intervention with the continuous feedback will last 12 months.

**Figure 2 F2:**
[figure not shown]
**Time frame**.

### Data collection

For this study we will develop a pool of 108 example cases (pictures of skin lesions we know the diagnosis, supplemented with short histories), 36 cases at a high difficulty level, 36 cases at a medium difficulty level and 36 cases at a low difficulty level. The levels of difficulty will be defined by two Dermatologists independently. For each of the three picture scoring sessions (at T_0_, T_1 _and T_2_), we will randomly allocate 36 cases (12 at each level of difficulty). This random distribution will be made prior to the start of the study to assure an equal difficulty of each picture scoring session.

With the scoring session prior and after the intervention, we measure the competence in skin cancer diagnosis of all participating GPs. We will record the percentage of correct diagnoses made on the basis of pictures with a short history. The GPs will have to score the likelihood of malignancy on a VAS ("very unlikely" to "very likely").

From photographed patients in the GPs' practices of the intervention group, we will record some demographic and clinical information (age, sex, skin type, parts of the body that were examined and the histology of skin lesions that were excised). All patient data are made anonymous and the encoding list is kept by the GP.

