**Methods/Design:**

*Design: *Randomised controlled trial (RCT).

*Population: *60 GPs, randomised into intervention group and control group.

*Intervention: *GPs get a Lumio loupe, a digital camera and continuous feedback based on pictures of skin lesions they send to the Dermatologist.

*Primary outcome: *Competence in the diagnosis of skin cancer by GPs, measured as the percentage of correctly classified pictures of skin lesions.

*Measurements: *At baseline, and prior to any intervention (T_0_), GPs will be asked to rate 36 pictures of skin lesions according to their likelihood of malignancy on a visual analogue scale (VAS). After a full day training course with both groups (T_1_) and after one year of continuous feedback (T_2_) with the intervention group, we will repeat the picture scoring session with both groups, using new pictures.

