### Analysis

Prior to the start of the study, the pictures will be categorised by two Dermatologists independently into three different levels of difficulty (low, medium or high level of difficulty). For every level of difficulty, a cut-off on the VAS will be defined previously to determine the correctness of the answers. This allows analysing the answers corrected for the difficulty of the pictures.

The Chi-square test will be used for the primary outcome. The presentation of the data will follow the CONSORT-recommendations for reporting results of randomised controlled trials [7].

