## Discussion

As shown in Figure 3 we expect an improvement of the competence in skin cancer diagnosis after the full day training course at T_1 _compared to T_0 _in both groups. This improvement will probably fade away in the control group after one year. It is known from different studies [8,9] that the effect of a continuing medical education (CME) is superior to the effect of single interventions. Therefore, we expect at T_2 _a significant difference in the competence in the diagnosis of skin cancer between the intervention group and the control group. We even expect that in the intervention group, GPs will score better at T_2 _than they did at T_1_, this would show the effect of the continuous problem based teaching.

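### One random draw by difficulty level does not assure equally hard picture sets, so changes over T0, T1 and T2 within an arm are confounded with the picture set; the between-arm contrast at T2 is not

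*Protocol article*

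**What the plan says.** The relevant statements are in four places.

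- **Data collection.** "For this study we will develop a pool of 108 example cases", 36 at each of three difficulty levels. Each of the three sessions receives 36 of them at random, 12 per level. On the purpose of the draw: "This random distribution will be made prior to the start of the study to assure an equal difficulty of each picture scoring session". On the labels: "The levels of difficulty will be defined by two Dermatologists independently".
- **Abstract, Methods/Design.** After the course and again after one year, "we will repeat the picture scoring session with both groups, using new pictures".
- **Analysis.** "For every level of difficulty, a cut-off on the VAS will be defined previously to determine the correctness of the answers". This is presented as correcting the answers for picture difficulty.
- **Discussion.** Four results are expected: a gain from T0 to T1 in both groups; a later loss in controls ("This improvement will probably fade away in the control group after one year"); a difference between the groups at T2; and a T2 score above the T1 score in the intervention group, of which it is said that "this would show the effect of the continuous problem based teaching".

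**The concern.** A single random split, stratified by a coarse expert label, makes the number of pictures per label equal across sessions. It does not make the sets equally hard for GPs. Pictures within one level still differ in difficulty, the label is a dermatologist's judgement rather than observed GP performance, and the draw as described is not balanced on whether the lesion is malignant or benign, although likelihood of malignancy is what GPs rate.

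If each set belongs to one time point, a harder or easier set looks exactly like forgetting or learning. The article nevertheless treats equality as assured and reads a within-arm rise from T1 to T2 as evidence for the teaching. At stake is the interpretation of the time courses, not the randomised comparison.

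**Working it through.** **1. Is set tied to time?** Reproducing the plan's count: 3 sessions x 36 = 108 pictures, and 3 x 12 = 36 per level. The three sets are disjoint and use up the pool, so each picture belongs to one session. That all GPs score the same 36 at a session is not stated word for word. It follows from the pool size, from allocation of cases to sessions rather than to GPs, and from the absence of any rotation. Set and time point are then completely aliased, with no further assumption needed.

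**2. Does the VAS cut-off help?** It is fixed per difficulty level. The same three cut-offs apply at T0, T1 and T2, so they cannot absorb differences between sets in the pictures within a level.

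**3. How far apart could two sets be?** Let s be the SD, within a level, of the true proportion of GPs who classify a picture correctly. The document gives no value; 0.05 to 0.25 is assumed. For two disjoint sets with 12 pictures from each of three levels:

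SD(difference of set means) = s x sqrt(2/36); 95% limits = 1.96 x that SD.

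| s (assumed) | SD of difference (points) | 95% limits (points) |
|---|---|---|
| 0.05 | 1.2 | +/-2.3 |
| 0.10 | 2.4 | +/-4.6 |
| 0.15 | 3.5 | +/-6.9 |
| 0.20 | 4.7 | +/-9.2 |
| 0.25 | 5.9 | +/-11.5 |

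Simulating the split (36 pictures per level into three groups of 12) gave SDs of 1.2, 2.3, 3.6, 4.8 and 5.9 points, in agreement.

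**4. True status.** If half of the 108 pictures are malignant (assumed), the number in a set of 36 is approximately hypergeometric (108, 54, 36): mean 18, SD = sqrt(36 x 0.5 x 0.5 x 72/107) = 2.46, 95% range 13 to 23.

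**5. What this would do to a within-arm test (illustration only).** Assume 65% correct, no true change, 27 to 30 GPs per arm, and a nominal 5% test that treats the pictures as fixed. With SE^2 = 2 x (0.65 x 0.35 - s^2)/(36 x n), the rejection rate is 2 x [1 - Phi(1.96 x SE / sqrt(SE^2 + 2s^2/36))]. It is about 9% at s = 0.05, 33-34% at s = 0.15 and 56-58% at s = 0.25.

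**6. The between-arm contrast.** At T2 both arms score the same set, so its difficulty enters both means and drops out of their difference. The same holds for the between-arm difference in T1-T2 change. A simulation with 27 GPs per arm, a GP SD of 5 points and a picture SD of 10 or 20 points gave a bias of about 0 (-0.01 and -0.13 points) and a false-positive rate of 4.7% in both cases.

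**The case against.** The strongest reply is that the trial's question is untouched. The hypothesis concerns feedback against control, arms are allocated after T1, and both arms see the same pictures at T2. The only analysis the article names is the test of the primary outcome. No within-arm test is specified, so the rejection rates in step 5 belong to an analysis the document does not state. The control arm also supplies what is needed to remove the set effect from the T1-T2 change. All of this stands. A reader might infer that the primary comparison is biased; the documents do not support that.

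The size also rests on assumptions. The within-level SD and the malignant fraction are not in the document. It is tempting to set the chance differences against a planning effect of 13 points, but the Sample Size section cites an improvement of about 13-36% from earlier work, does not say that these are percentage points, and assumes a larger effect here. The figure is at most a rough yardstick.

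Finally, the protocol does take difficulty seriously, through stratification and the cut-offs. That reduces imbalance between sets but does not remove it, and the objection does not rescue two things the article says outright: that equality is assured, and that a within-arm rise would show the teaching effect.

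**Conclusion.** The concern holds for changes over time within an arm. Three of the four expected results (gain T0 to T1, fading in controls, further gain T1 to T2 in the intervention arm) cannot be separated from differences between picture sets. The fourth, the between-arm difference at T2, is unaffected.

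The aliasing follows from the design as described, given one set per session for all GPs. Its size depends on the assumed within-level SD: about +/-2 to +/-12 points (95% limits) for SDs of 5 to 25 points. Nothing in the document shows that the sets will in fact be unequal by any given amount; what is wrong is the claim that equality is assured and the causal reading built on it. This should be corrected, but it does not threaten the main result.

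**What to change.** 1. **Discussion.** Judge the feedback effect by the between-arm difference at T2 adjusted for T1, or by the between-arm difference in T1-T2 change. Call within-arm time trends descriptive. Delete the statement that T2 above T1 in the intervention arm would demonstrate the effect of teaching. Cost: a change of text; the planned data suffice.

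2. **Data collection.** Draw the three sets stratified by difficulty level and by true status (malignant or benign). Replace the word *assure* with a statement that sets are balanced on level and true status only. Cost: almost none, since the diagnosis of every picture in the pool is known and the draw precedes the study. Exact balance needs a multiple of three malignant pictures in each level.

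3. **Optional, if interpretable time trends are wanted.** Rotate the sets over the time points (orders ABC, BCA, CAB; 60/3 = 20 GPs each), stratify arm allocation by order, and include set in the model. Order can be assigned before T0, because arms are allocated only after T1. No extra GPs or pictures are needed, but each session needs three booklets. Pictures seen by some GPs at T0 or T1 would also be scored by others at T2 and could leak into the primary endpoint, which new pictures now protect. Even with rotation, T0 to T1 remains an uncontrolled before-after change.

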### Analysis

Prior to the start of the study, the pictures will be categorised by two Dermatologists independently into three different levels of difficulty (low, medium or high level of difficulty). For every level of difficulty, a cut-off on the VAS will be defined previously to determine the correctness of the answers. This allows analysing the answers corrected for the difficulty of the pictures.

The Chi-square test will be used for the primary outcome. The presentation of the data will follow the CONSORT-recommendations for reporting results of randomised controlled trials [7].

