### Sample Size

The power calculation was based on data from previous studies, as e.g. Gerbert et al. [6] who showed that the improvement in correct answers with an educational intervention could be about 13-36%. Due to the continuous feedback via teledermatology we assume this effect even to be greater.

Based on these assumptions, a power of 80% and a significance level of 5% (alpha error) the sample size has to be 53 GPs. With a drop out rate of 10% we concluded that 60 GPs would be necessary.

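### The Chi-square test fixed for the primary outcome cannot use each GP's T0 and T1 scores, which gives up precision of uncertain size

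*Protocol article*

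**What the plan says.** The Analysis section names one test: "The Chi-square test will be used for the primary outcome". The only correction it mentions is for the difficulty of the pictures. It assigns no role to a GP's own earlier scores.

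The Procedure section has GPs in both groups score pictures at T0, at T1 after the common course, and at T2 after the feedback year. According to Data collection, each session uses 36 cases, 12 per difficulty level, randomly assigned to sessions so that difficulty is equal. The same section says: "With the scoring session prior and after the intervention, we measure the competence in skin cancer diagnosis of all participating GPs".

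On timing, Randomisation and Blinding states: "After the initial picture scoring sessions and the full day training course, we will draw up a randomisation list by computer". The word for sessions is plural there and in the descriptions of both groups. This places T0 and T1 before allocation. The Discussion expects the difference between arms at T2.

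**The concern.** Each GP apparently supplies 2 × 36 = 72 ratings before allocation, on the construct and metric compared at T2. Scores of this kind are natural covariates. They cannot be affected by the arm, and whatever they explain of the T2 variation between GPs comes out of the error term. That the pictures differ between sessions does not disqualify them, because they are recorded before allocation and on the same metric.

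A Chi-square test has no place for them. The article fixes that test, so this is more than a detail left to an analysis plan: a later plan could adjust only by replacing the named test. At stake is power in a trial of 60 GPs, and a T2 estimate that carries part of any chance difference in skill between the arms.

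**Working it through.** **The plan's own figure.** Sample Size says "the sample size has to be 53 GPs" and then "With a drop out rate of 10% we concluded that 60 GPs would be necessary". The inflation is consistent: 53/(1 − 0.10) = 58.9, so 59, and the stated 60 is close. The 53 itself cannot be reproduced, because the article gives a range of improvements but no control percentage, SD or single design effect. So 53 GPs at 80% power is taken as a yardstick.

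**Inputs.** From Sample Size: 53 evaluable GPs, 80% power, 5% significance. Assumed: two-sided test, 1:1 allocation (26.5 per arm), and r, the correlation between one earlier score and the T2 score.

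**Unadjusted GP-level comparison** (normal approximation). Detectable difference = (1.960 + 0.842) × √(2/26.5) = 2.802 × 0.2747 = 0.77 SD.

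**Adjusting for one earlier score.** The residual variance is multiplied by 1 − r². Detectable difference = 0.77 × √(1 − r²). Power at 0.77 SD = Φ(2.802/√(1 − r²) − 1.960). Equivalent unadjusted N = 53/(1 − r²). A T1 imbalance of 0.3 SD shifts the unadjusted T2 difference by 0.3 × r.

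| r (assumed) | 1 − r² | Detectable difference (SD) | Power at 0.77 SD | Equivalent N | T2 shift from 0.3 SD at T1 |
|---|---|---|---|---|---|
| 0.3 | 0.91 | 0.73 | 84% | 58 | 0.09 SD |
| 0.5 | 0.75 | 0.67 | 90% | 71 | 0.15 SD |
| 0.6 | 0.64 | 0.62 | 94% | 83 | 0.18 SD |
| 0.7 | 0.51 | 0.55 | 98% | 104 | 0.21 SD |

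**Adjusting for both scores.** If T0, T1 and T2 are all equally correlated, R² = 2r²/(1 + r). This gives 0.138, 0.333, 0.450 and 0.576, and power of about 86%, 93%, 96% and 99%.

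**How low r could be.** Assume 70% correct. Sampling noise on 36 pictures is √(0.7 × 0.3/36) = 7.6 percentage points. With perfectly stable skill and a between-GP SD of s points, r = s²/(s² + 7.6²). For s = 5, r = 25/(25 + 58) = 0.30. An r of 0.5 needs s of about 7.6, and an r of 0.7 needs about 11.7.

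**Simulation check.** This used 53 GPs with 36 pictures each and assumed between-GP SDs of 0.3 to 0.7 on the logit scale. A t-test on GP percentages was compared with ANCOVA on T0 and T1. Power was 75% against 79% at an observed T1–T2 correlation of 0.29, 53% against 65% at about 0.45, and 33% against 66% at 0.70. Type I error was near 5% for both.

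**The case against.** The strongest objection is that the yardstick is not the plan. The article plans a Chi-square test and gives no SD, so the power figures do not measure what this trial would lose under its own test. This stands: they show what the earlier scores are worth once the analysis is at GP level. If the Chi-square test pools pictures over GPs, it also ignores clustering. That is a separate fault, with a simulated false-positive rate of 13% to 35% in the same scenarios, and its repair already requires another test.

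Second, r may be low. The scores rest on 36 items, the pictures are new each time, T2 follows about a year after the course, and the Discussion expects the course effect to fade in controls. This stands too. The article does not support a claim that the earlier scores predict T2 strongly, and at r = 0.3 the gain is only about four percentage points of power.

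Third, a reader might infer that the unadjusted comparison is biased, or that a T1 imbalance passes in full into T2. Neither follows. Under randomisation, chance imbalance is part of the ordinary standard error, the overall type I error is unaffected, and only the fraction r carries over.

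A reader might also fault the absence of stratification by score. A condensed article may leave that out, so it is not part of this point.

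What the objections do not remove is that the named test excludes covariates that every GP supplies.

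**Conclusion.** The point holds as a loss of precision of uncertain size, not as a threat to validity. Against an unadjusted GP-level comparison with 80% power at 53 GPs, adjusting for one earlier score would give about 84% to 98% power over r = 0.3 to 0.7.

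This rests on assumptions. The value of r, the two-sided test and 1:1 allocation are not in the article. T2 as the time of the primary comparison is inferred from the Procedure and Discussion sections, because Primary outcome names none. That T1 scoring precedes allocation rests on the plural for the scoring sessions, and the study-design and time-frame figures are not available to confirm it. The existence of the gain is well supported unless r is close to zero; its size is not.

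**What to change.** Replace the Chi-square sentence in Analysis with a prespecified GP-level ANCOVA of percentage correct at T2 on arm, T1 score and T0 score. Alternatively, specify a mixed logistic model of the picture-level answers at T2 with a random effect for GP and the same covariates. Either also makes the GP the unit of inference. State T2 as the time point, and confirm in Randomisation and Blinding that T1 scoring is complete before the list is drawn up.

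The cost is two degrees of freedom and a change of analysis wording; no new data or sessions are needed. The change should be made before outcome data are seen, so that the adjustment cannot look post hoc.

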### Ethical principles

The study is being conducted in accordance with medical professional codex and the Helsinki Declaration as of 1996 as well as Data Security Laws and Good Clinical Practice criteria (GCP). Study participation of GPs and patients is voluntary and can be cancelled at any time without provision of reasons. The study protocol will be registered at a trial register (current-controlled-trials) and the study protocol will be published in an open access journal, to be accessible for everybody.

#### GP and patient informed consent

Previous to study participation GPs receive written and spoken information about the content and extent of the planned study. In case of acceptance they sign the informed consent form. Written informed consent will also be obtained from patients prior to take pictures of one of their skin lesions. In case of study discontinuation all material will be destroyed or the GPs and patients will be asked if they approve existing material for analysis in the study.

#### Vote of the ethics committee (KEK-ZH-Nr. 2010-0384/5)

The study protocol has been approved by the ethics committee of Zurich. A written and unrestricted positive vote of the ethics committee was recorded on the 1^st ^of March 2011.

#### Data security and disclosure of original documents

The GP and patient names, pictures of skin lesions and all other confidential information fall under medical confidentiality rules and are treated according to appropriate Federal Data Security Laws. All study related data and documents are stored on a protected central server of the University of Zurich. Only direct members of the internal study team can access the respective files. Intermediate and final reports are stored at the Institute of General Practice and at the Department of Dermatology at the Zurich University Hospital (USZ).

## Discussion

As shown in Figure 3 we expect an improvement of the competence in skin cancer diagnosis after the full day training course at T_1 _compared to T_0 _in both groups. This improvement will probably fade away in the control group after one year. It is known from different studies [8,9] that the effect of a continuing medical education (CME) is superior to the effect of single interventions. Therefore, we expect at T_2 _a significant difference in the competence in the diagnosis of skin cancer between the intervention group and the control group. We even expect that in the intervention group, GPs will score better at T_2 _than they did at T_1_, this would show the effect of the continuous problem based teaching.

**Figure 3 F3:**
[figure not shown]
**Expected results**.

## Limitations of the study

With our study, we do not investigate the influence of our intervention on the mortality caused by skin cancers. Additionally, blinding of GPs is not possible.

## List of abbreviations

BCC: basal cell carcinoma; GP: general practitioner; NMSC: nonmelanoma skin cancer; SCC: squamous cell carcinoma; VAS: visual analogue scale

